### 4.2 Blinding (Masking)

This study is open-label due to the nature of the interventions—ICE and TEE are procedurally distinct and cannot be blinded to operators or patients. However, to minimize bias:

- The Clinical Endpoint Committee (CEC) is blinded to group assignment when reviewing clinical outcomes related to thromboembolic and bleeding events.
- Statistical analysts will also remain blinded to group allocation during primary endpoint analysis.

No blinding is implemented for care providers or procedural staff due to the technical impossibility and potential risk to procedural safety.

### 4.3 Implementation

- The randomization sequence is generated centrally by the study's data coordination center.
- Site investigators are responsible for enrolling eligible participants and confirming inclusion/exclusion criteria.

415       • Random assignment is implemented electronically through the electronic data  
416       capture (EDC) system, which automatically provides allocation after patient  
417       registration.

418 All randomization actions are timestamped and logged within the EDC system to  
419 ensure traceability and compliance.

420

## 421 **5. Methods: Data Collection, Management, Quality** 422 **Control and Analysis**

### 423 **5.1 Data Collection Methods**

424 All patient data are recorded using a secure electronic Case Report Form (eCRF)  
425 system. Data collection is performed by trained investigators at each participating  
426 center and includes:

#### 427 **Baseline Data**

- 428       • Demographics: age, sex, height, weight, blood pressure
- 429       • Medical history: cardiovascular disease, non-cardiac comorbidities
- 430       • AF history: date of onset, type (paroxysmal/persistent), CHA2DS2-VASc score
- 431       • Medications: antiarrhythmic drugs, anticoagulants
- 432       • Echocardiographic parameters: LVEF, left atrial diameter
- 433       • ECG: heart rate, rhythm

#### 434 **Procedural Data**

- 435       • Imaging modality used (ICE or TEE)
- 436       • Imaging views and interpretation
- 437       • Mapping system and catheter type
- 438       • Transseptal puncture method and anticoagulation strategy
- 439       • Radiofrequency power, ablation duration, lesion characteristics

#### 440 **Outcome and Follow-Up Data**

- 441       • Thromboembolic events (stroke, TIA, systemic embolism)
- 442       • Complications: bleeding, tamponade, vascular injury
- 443       • Pain and anxiety scores (NRS and HADS)
- 444       • Hospitalization cost and duration
- 445       • Follow-up visits at 1 week, 2 weeks, and 1 month post-procedure

- Adverse events and serious adverse events (SAEs)

All collected data are entered in real time or within 14 days of each study visit, and validated by the site principal investigator.

## 5.2 Data Management

A central **data management team** oversees the trial-wide eCRF system. The following procedures are in place:

- **Data entry validation:** automated logic and range checks within the eCRF system
- **Source data verification:** routine site monitoring by CRO staff
- **Data security:** encrypted server storage with access limited to authorized personnel
- **Audit trail:** all modifications timestamped and traceable
- **Missing data protocol:** queries issued and resolved in collaboration with local site staff

All data will be locked prior to final analysis after resolving outstanding queries. Patient confidentiality is protected throughout by anonymization and secure data handling procedures.

## 5.4 Quality Control

To ensure the validity and consistency of thrombus assessment by ICE and TEE, the following quality control measures are implemented:

### Standardized Imaging Protocols

- All participating sites are required to follow a unified imaging acquisition protocol for both intracardiac echocardiography (ICE) and transesophageal echocardiography (TEE), based on current international guidelines.
- For ICE, standardized views from the pulmonary artery (PA) or right ventricular outflow tract (RVOT) are mandated for optimal visualization of the left atrial appendage (LAA).
- For TEE, imaging is performed at multiple standard angles (0°, 45°, 90°, 135°) to comprehensively assess the LAA.

### Operator Training and Credentialing

- All echocardiographers and electrophysiologists involved in image acquisition and interpretation received centralized training before study initiation.
- Competency was verified through practical assessment and review of sample cases to ensure proficiency with both ICE and TEE modalities.

#### **Blinded Independent Image Interpretation**

- All TEE and ICE images are independently reviewed by at least two experienced echocardiographers who are blinded to group assignment and to each other's assessments.
- In cases of disagreement, a third independent reviewer adjudicates the final interpretation.
- Image reviewers are unaware of patients' clinical outcomes to prevent interpretation bias.

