## 2.3 Trial Design

This study is a multicenter, prospective, randomized, open-label, parallel-group, non-inferiority trial. A total of 1810 patients undergoing AF ablation were randomized 1:1 to receive either ICE-guided or TEE-guided thrombus screening. Outcome assessors, including the Clinical Endpoint Committee (CEC), are blinded to group allocation.

[figure not shown]

Figure 1. Trial design

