### 325 **TEE Group (Control Arm)**

- 326           • Thrombus screening performed within 24 hours pre-procedure using standard  
327           TEE (GE Vivid E9 or Philips iE33).
- 328           • Multiplanar views including mid-esophageal four-chamber view, mid-  
329           esophageal two-chamber view, mid-esophageal long-axis view, transgastric  
330           short-axis view, deep transgastric long-axis view and upper esophageal aortic  
331           arch view.
- 332           • Transseptal puncture guided by fluoroscopy.

333

334 TEE images were first evaluated by an experienced echocardiographer and  
335 subsequently reviewed by at least two other experienced echocardiographers who  
336 were blinded to the results of the initial TEE. This meticulous procedure ensures  
337 comprehensive cardiac assessment and quality control through multiple expert  
338 reviews.

339

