## 4. Methods: Assignment of Interventions

### 4.1 Allocation

This study employs a **simple computerized randomization** strategy with a 1:1 allocation ratio. Eligible participants are randomly assigned to undergo thrombus screening with either ICE (ICE group) or TEE (TEE group) before catheter ablation.

The randomization schedule is generated using validated, centralized computer software to ensure adequate allocation concealment. Allocation occurs **after patient enrollment and informed consent**, and prior to the start of imaging and ablation procedures.

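### Image readers cannot be blinded to group as the protocol states, because the imaging modality is the randomised group; the thrombus-detection comparison should be described as not blinded to modality

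*Protocol*

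**What the plan says.** Four parts of the protocol bear on who is masked to what.

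- Section 5.4 Quality Control, under Blinded Independent Image Interpretation: "All TEE and ICE images are independently reviewed by at least two experienced echocardiographers who are blinded to group assignment". The same list keeps the two readers unaware of each other's reads, has a third reader settle disagreements, and keeps readers unaware of clinical outcomes.
- Section 2.3 Trial Design: "Outcome assessors, including the Clinical Endpoint Committee (CEC), are blinded to group allocation".
- Section 4.2 Blinding: the trial is open-label because "ICE and TEE are procedurally distinct and cannot be blinded to operators or patients". The blinded parties it lists are the Clinical Endpoint Committee (CEC) and the statistical analysts. Image readers are not on the list.
- Section 3.4, TEE Group: a first echocardiographer reads the TEE study, and at least two others review it without knowing that first result. No masking to group is mentioned there, and the ICE Group text describes no corresponding review.

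The thrombus detection rate is a secondary endpoint in Section 3.5. Section 5.4 Statistical Methods names it among the categorical variables compared between groups by a chi-square or Fisher's exact test.

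**The concern.** Masking to group means that the assessor cannot tell the arm from the material being assessed. Here that material is the screening study, and the arms differ by the type of screening study. The protocol thus claims a safeguard that its own design rules out.

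At stake is how the thrombus-detection result may be read. Finding or excluding thrombus is partly a matter of judgement when image quality is poor. A reader who expects one modality to see better, or to produce more artefact, may resolve uncertain images differently by modality, and hence by arm. A second reader and a third-reader adjudication do not remove an expectation that all readers share. Someone who takes the blinding statement at face value would discount this bias. The endpoint matters because the objective in Section 2.2 is framed as non-inferiority in excluding left atrial or appendage thrombus.

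**Working it through.** No power, margin or event-rate calculation applies. The check sets the protocol's statements side by side.

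1. **What defines the group.** Section 4.1: "Eligible participants are randomly assigned to undergo thrombus screening with either ICE (ICE group) or TEE (TEE group) before catheter ablation". Modality and group are the same variable.
2. **Whether either arm has both studies.** None is described. Section 3.4 gives ICE imaging for the ICE arm and TEE for the TEE arm, and in the TEE arm the puncture step reads "Transseptal puncture guided by fluoroscopy".
3. **Whether the images look alike.** The required acquisitions differ. Section 5.4, Standardized Imaging Protocols: "For ICE, standardized views from the pulmonary artery (PA) or right ventricular outflow tract (RVOT) are mandated". TEE is acquired at a set of standard probe angles.
4. **Whether readers can tell them apart.** Training covers image interpretation as well as acquisition, with competency checked to "ensure proficiency with both ICE and TEE modalities".
5. **Whether modality is hidden from readers.** No section describes a way of doing so, and removing names or site labels would not, since the image content itself reveals the modality.

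From 1 to 5, the reader knows the modality, the modality is the arm, and so the reader knows the arm. The other items of masking do not depend on modality and remain feasible: to the initial or site read, to the other reader, and to clinical outcomes.

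**Which read feeds the endpoint.** The protocol does not say whether the detection rate uses the site read or the independent review. If it uses the site read, the operator is unblinded by Section 4.2. If it uses the independent review, steps 1 to 5 apply. The endpoint is not blinded to group in either case.

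**What the planned sensitivity analysis shows.** The Subgroup and Sensitivity Analyses text excludes equivocal imaging cases. In one arm, let d be the proportion read as thrombus and e the proportion read as equivocal.

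- Equivocal counted as negative: d
- Equivocal counted as positive: d + e
- Equivocal excluded: d / (1 − e)

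The excluded value always lies between the other two, because (d + e)(1 − e) − d = e(1 − d − e) ≥ 0. Exclusion therefore gives one value inside the range and does not show how wide the range is. Counting both ways shows the full width, e, separately in each arm.

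**The case against.** The case on the other side has real force on several points.

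- **The primary result is untouched.** Section 2.1 deliberately chooses embolic events over thrombus detection and treats thrombus as a surrogate. The non-inferiority decision uses no image read. This stands, and it limits the importance of the point.
- **The CEC's blinding is not refuted.** A reader might infer that, because image readers know the arm, the outcome-assessor claim in Section 2.3 fails and the primary endpoint is compromised. The documents do not support that. Section 4.2 confines the committee's blinding to thromboembolic and bleeding events, and Section 6.1 gives it de-identified event summaries with relevant imaging, not stated to include the screening study. The fault in Section 2.3 is only that its wording is open enough to be read as covering image readers.
- **No section expressly calls the detection endpoint blinded.** True. The claim attaches to the readers, under a quality-control heading, and its extension to the endpoint is an inference. The reader statement is nevertheless wrong as written.
- **The background figures do not size the bias.** Section 2.1 cites equivocal TEE of up to 17.8% and thrombus in 0.4% to 15.2% of anticoagulated patients. With 1810 / 2 = 905 per arm, it is tempting to set 905 × 0.178 ≈ 161 equivocal reads against 905 × 0.004 ≈ 4 to 905 × 0.152 ≈ 138 thrombi. This should not be done: the 17.8% is a reported maximum for TEE alone, no ICE rate is given, and the comparison shows neither how many reads would change nor in which direction.
- **Safeguards exist.** Standard views, verified competency, two independent readers, adjudication, an imaging-quality subgroup and the exclusion analysis all help. They reduce error, but they do not make readers unaware of modality.
- **Recognising the modality is inherent in the comparison.** It is, so rewording will not remove the bias. That is a reason to describe the endpoint accurately.

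**Conclusion.** The statement that image readers are blinded to group is wrong as written, since the design cannot deliver it. The between-arm comparison of thrombus detection must be treated as not blinded to modality, whichever read it uses. The imaging-quality subgroup and the exclusion of equivocal cases share this limit in so far as they rest on the same reads.

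The effect is confined to image-based results. No number can be put on it, because the protocol gives no between-arm difference in equivocal reads. The importance is moderate to low: a false description of masking on a secondary endpoint, inexpensive to correct, with no bearing on the primary non-inferiority test.

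The conclusion assumes that each patient has a screening study of one modality only, as the protocol describes, and that an echocardiographer proficient in both can recognise which one is on the screen.

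**What to change.** 1. In Section 5.4, Blinded Independent Image Interpretation, replace the claim of masking to group. State that readers are masked to the initial or site read, to the other reader's assessment and to clinical outcomes, but not to modality.
2. Reconcile this with the TEE Group text in Section 3.4, which masks reviewers only to the first TEE result, and with Section 4.2, which does not list image readers among the blinded parties.
3. In Section 2.3, make clear that outcome assessors does not include image readers.
4. Describe thrombus detection as not blinded to modality wherever it is defined or reported.
5. Besides the planned exclusion analysis, report the detection rate by arm with equivocal reads counted as negative and then as positive. These bounds cover only images that readers label equivocal; they do not show leaning within reads recorded as definite.

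The cost is wording in a few sections, one additional table, and the loss of the blinded label for this endpoint. Sample size and the primary analysis are unaffected.

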### **5.4 Statistical Methods**

#### **Primary Analysis Population**

- Modified intention-to-treat (mITT): all randomized patients who underwent ablation
- Per-protocol (PP): patients who completed imaging and ablation per assigned group without major protocol violations

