## 2. Introduction

### 2.1 Background and Rationale

Atrial fibrillation (AF) is the most common sustained cardiac arrhythmia, characterized by rapid and irregular atrial electrical activity. This disrupts effective atrial contraction and hemodynamics, leading to blood stasis in the left atrial appendage (LAA) and significantly increasing the risk of thrombus formation. Studies have shown that the incidence of LAA thrombi in anticoagulated patients with AF ranges from 0.4% to 15.2%, depending on individual characteristics and comorbidities. The presence of LAA thrombus is considered an absolute contraindication to catheter ablation. Once detected, the procedure must be postponed until adequate anticoagulation therapy has resolved the thrombus.

Transesophageal echocardiography (TEE) has long been regarded as the gold standard for preprocedural LAA thrombus screening, with a reported sensitivity and specificity exceeding 90%. TEE enables high-resolution imaging by positioning an ultrasound probe in the esophagus, close to the heart. In a global survey of AF ablation centers, 73.2% reported routine use of TEE before ablation, regardless of patients' CHA2DS2-VASc scores. However, despite its diagnostic accuracy, TEE is semi-invasive and associated with discomfort and procedural risks such as gag reflex, sedation-related complications, and even esophageal injury. Additionally, when image quality is suboptimal, the sensitivity of TEE to exclude LAA thrombi is reduced. The proportion of equivocal TEE findings has been reported to be as high as 17.8%, leading to potential misdiagnosis and procedural delays.

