## Secondary Endpoints

The prespecified secondary endpoints include:

- The detection rate of thrombus.
- Death related to the radiofrequency ablation procedure.
- Major bleeding complications: pericardial effusions and cardiac tamponade.
- Minor bleeding complications: vascular complications such as pseudoaneurysms, arterio-venous fistulas, and hematomas.
- Procedural characteristics: total procedure time, fluoroscopy time, and radiofrequency delivery time.
- Pre-procedural psychological state: Assessed using the Hospital Anxiety and Depression Scale (HADS), 14a self-assessment questionnaire measuring anxiety and depression levels in patients receiving medical care. Higher scores indicate more severe symptoms.
- Procedural pain degree: Measured using the Numeric Rating Scale (NRS), where patients rate their pain on a scale from 0 (no pain) to 10 (worst possible pain).
- Hospitalization cost: Expenses incurred during a patient's hospital stay, including charges for medical services, procedures, medications, accommodations, and other related expenses.
- Preprocedural waiting time: The period of time a patient waits before undergoing ablation.

These well-defined endpoints will help the researchers assess the effectiveness, safety, and patient experience of using ICE compared to TEE in patients undergoing AF ablation.

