## 516 **Missing Data**

- 517 • Primary endpoint: patients lost to follow-up before event occurrence will be  
518 excluded from the per-protocol analysis
- 519 • Sensitivity analyses with imputation may be performed as needed

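### Both primary analysis sets require ablation, which the randomised scan itself helps decide; never-ablated patients have no analysis set and no outcome schedule

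*Protocol*

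**What the plan says.** Section 5.4 (Statistical Methods), under Primary Analysis Population, gives two sets: "Modified intention-to-treat (mITT): all randomized patients who underwent ablation" and "Per-protocol (PP): patients who completed imaging and ablation per assigned group without major protocol violations". The protocol defines no other set.

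Three other places bear on these definitions:

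- Section 4.1 (Allocation) places randomisation after consent "and prior to the start of imaging and ablation procedures".
- Section 2.1 (Background and Rationale) states: "The presence of LAA thrombus is considered an absolute contraindication to catheter ablation". It continues: "Once detected, the procedure must be postponed until adequate anticoagulation therapy has resolved the thrombus".
- Section 5.1 (Outcome and Follow-Up Data) schedules "Follow-up visits at 1 week, 2 weeks, and 1 month post-procedure". It gives no schedule for a patient who has no procedure.

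Section 3.5 lists "The detection rate of thrombus" first among the secondary endpoints. Section 5.4 (Secondary Endpoint Analysis) gives it a chi-square or Fisher test and names no population for it.

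**The concern.** The randomised intervention is the screening scan, and whether the patient goes on to ablation is partly its result. A set restricted to ablated patients therefore selects on something that happens after randomisation and depends on the modality under test. This differs from the usual modified intention-to-treat exclusion of patients who never started the assigned intervention, because here the assigned scan has already been done. If the two modalities detect thrombus at different rates, the patients left in the two arms differ in composition, and the comparison is no longer the one that was randomised.

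Two things are at stake. The primary contrast omits embolic events in patients who are never ablated. The detection endpoint, which is the most direct measure of the objective in section 2.2, may also lose its positive cases.

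**Working it through.** **Inputs from the protocol.** 1810 patients randomised 1:1 (section 2.3), so 905 per arm. Expected event rates 0.6% (ICE) and 0.5% (TEE), margin 0.8%, one-sided alpha 0.025, dropout 2% (section 3.2). Thrombus incidence 0.4% to 15.2% in anticoagulated patients (section 2.1). Farrington-Manning 95% interval for the risk difference (section 5.4).

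**The plan's own figure.** 7.84 × 0.010939 / 0.000049 = 1750.24 (printed as 1750.45), and 1750 / 0.98 = 1786 after rounding up. Both reproduce, and nothing in this point alters them.

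**Step 1: patients who could leave the sets.** Loss per arm = 905 × proportion with a detected thrombus, if none is ablated later:

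| Detected | Loss per arm |
|---|---|
| 0.4% | 905 × 0.004 = 3.6 |
| 2% | 905 × 0.02 = 18.1 |
| 5% | 905 × 0.05 = 45.3 |
| 15.2% | 905 × 0.152 = 137.6 |

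These are upper bounds, because any patient ablated later may return to the set. Above 2% detection, losses on this scale would exceed the 2% dropout allowance by themselves. The same figures are the detected thrombi that would go uncounted if the detection endpoint were analysed in the ablated set.

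**Step 2: expected bias in the primary risk difference.** The protocol does not give the inputs for this, so the following are assumptions: sensitivity 80% in one arm and 95% in the other; 10% event risk when a patient is ablated with a missed thrombus; 0.5% event risk in patients without thrombus; event risk *e* of 0 to 5% in deferred patients, none of them ablated later. With thrombus incidence *t* and sensitivity *s*:

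- Events in ablated patients: E = (1 − t) × 0.005 + t(1 − s) × 0.10
- Rate in the ablated set: E / (1 − ts)
- Rate in all randomised: E + ts × e

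Example with t = 2%, e = 5%, ICE 80%, TEE 95%:

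- ICE: E = 0.0049 + 0.0004 = 0.0053. Ablated set 0.0053 / 0.984 = 0.5386%. All randomised 0.0053 + 0.016 × 0.05 = 0.610%.
- TEE: E = 0.0049 + 0.0001 = 0.0050. Ablated set 0.0050 / 0.981 = 0.5097%. All randomised 0.0050 + 0.019 × 0.05 = 0.595%.
- Risk difference: 0.0289 points in the ablated set, 0.0150 points in all randomised. The gap is 0.014 points.

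The largest gap over *e* from 0 to 5% is under 0.003 points at t = 0.4%, 0.014 at 2%, 0.037 at 5% and 0.13 at 15.2%. Swapping the sensitivities reverses the sign. With equal sensitivity the gap is nil.

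**Step 3: how much one event matters.** Expected events are 905 × 0.006 = 5.4 (ICE) and 905 × 0.005 = 4.5 (TEE). One event is 1/905 = 0.11 points. Farrington-Manning upper 95% limits for ICE minus TEE at 905 per arm:

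| ICE vs TEE events | Upper limit | Against 0.8% |
|---|---|---|
| 4 vs 4 | 0.740% | non-inferior |
| 5 vs 4 | 0.897% | not shown |

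One ICE-arm event in a patient outside the set is enough to move the result across the margin.

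**The case against.** Several stronger readings are tempting, and the text does not support them.

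- *Every patient with a detected thrombus drops out.* Section 2.1 speaks of postponement, not cancellation, and the modified intention-to-treat definition has no time limit. Read literally, a patient ablated after the thrombus has resolved is in the set. Only never-ablated patients are certain to leave.
- *The detection endpoint is empty by construction.* The two sets stand under a heading about the primary analysis, and no set is named for detection. A secondary denominator may also be fixed in the statistical analysis plan, which is not at hand. The loss follows only if the two sets govern this endpoint and postponed patients are not ablated later.
- *Embolic events during deferral go unseen.* Section 5.1 also collects adverse and serious adverse events, and section 6.1 has the endpoint committee adjudicate all suspected thromboembolic events. What is missing is a visit schedule and an analysis set for the never-ablated, not every route by which an event could be recorded.
- *Equivocal TEE scans, up to 17.8% in section 2.1, also remove patients.* The protocol does not say that such patients are deferred. Its planned sensitivity analysis without equivocal scans implies that they are otherwise in the analysed set.
- *The selection clearly favours non-inferiority.* The direction depends on which modality detects more, and the expected size is small. The upper end of the incidence range may also not apply here: the trial requires at least 3 weeks of uninterrupted anticoagulation and excludes severe heart failure and stroke or TIA within 6 months.

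It is also fair to say that an ablated set suits a periprocedural endpoint, and that adding patients with little procedural risk can pull the difference towards zero. That is a reason to keep the ablated set, but not to make ablation a condition of every defined analysis. The core of the point stands: randomisation precedes the scan, the scan affects who is ablated, and both sets require ablation.

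**Conclusion.** The point holds as a flaw in the population definitions that should be fixed. Inclusion in both primary sets depends on the result of the randomised test, and the protocol defines no all-randomised or all-screened set to set against them.

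For thrombus detection the possible loss is about 4 to 138 positives per 905 patients, conditional on the two sets governing that endpoint and on no later ablation. For the primary risk difference the expected bias is probably small: at most 0.014 points at 2% incidence under the stated assumptions, nil with equal sensitivity, and comparable to one event (0.11 points) only when thrombus is common and detection differs by arm. The reason to act on the primary endpoint is its fragility. With about 5 events expected per arm, one event outside the set can turn an upper limit of 0.740% into 0.897%. A reader might infer that the trial's conclusion is invalid, but the documents do not support that.

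**What to change.** Amend sections 3.5, 5.1 and 5.4 as follows:

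1. Add an analysis of the primary endpoint in all randomised patients, as assigned. Report it alongside the ablated and per-protocol sets and require the three to be consistent before non-inferiority is claimed.
2. Define an outcome window for patients whose ablation is postponed or cancelled. One workable form runs from randomisation to one month after the procedure, or to one month after the originally planned date if no ablation takes place.
3. State that an ablation done after postponement counts as ablation for the modified intention-to-treat set.
4. For thrombus detection, use all patients screened as assigned as the denominator. For hospitalisation cost, use all randomised patients.

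The cost is wording plus outcome status for the patients not ablated, from records or a telephone call. Sample size and treatment are unchanged. The downside is slight dilution. If never-ablated patients have no events, the assumed 0.1-point difference becomes 0.1 × 0.98 = 0.098 points with 2% never ablated, and 0.1 × 0.848 = 0.085 at 15.2%. This is why the ablated and per-protocol sets should stay.

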## 351 **3.5 Endpoints**

## Primary Endpoints

The primary endpoint centers on thromboembolic events occurring during the periprocedural period, which encompass:

- Stroke: Characterized as an abrupt onset of neurological dysfunction resulting from disrupted cerebral blood flow, causing tissue damage. Diagnosis is confirmed via MRI or CT imaging.
- Transient Ischemic Attack (TIA): A brief episode of neurological dysfunction due to temporary interruption of blood supply to a localized area of the brain. Symptoms typically resolve within 24 hours.
- Systemic Embolism: Sudden blockage of a blood vessel by an embolus, resulting in tissue ischemia or infarction in an organ other than the brain.

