#### **Primary Endpoint Analysis**

- Incidence of thromboembolic events will be compared between ICE and TEE groups.
- Analysis will use logistic regression to estimate the risk difference and 95% confidence interval.
- Non-inferiority is demonstrated if the upper bound of the 95% CI for the risk difference is below the predefined margin of 0.8%.
- The primary endpoint was evaluated using risk difference (RD) with Farrington – Manning 95% CI, and noninferiority was concluded if the upper CI limit was below the prespecified margin.

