## **8.2 Primary Study Endpoints Modification**

The primary study endpoints were adjusted from encompassing all complications to focus specifically on peri-procedural thromboembolic events (stroke, transient ischemic attack, and systemic embolism). Other non-thromboembolic complications (bleeding complications) were included as secondary study endpoints.

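### The per-protocol set requires completed ablation, so an embolic event that stops the procedure removes the patient from that set because of the primary outcome

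*Protocol*

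**What the plan says.** Section 5.4 Statistical Methods, under Primary Analysis Population, names two sets. The mITT set is "all randomized patients who underwent ablation". The PP set is "patients who completed imaging and ablation per assigned group without major protocol violations". The two entries use different verbs, and PP lists freedom from major violations separately, so completion is a requirement of its own.

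Section 3.5 says: "The primary endpoint centers on thromboembolic events occurring during the periprocedural period". The components are stroke, TIA and systemic embolism. Section 8.2 confirms that the rest moved out of the primary endpoint: "Other non-thromboembolic complications (bleeding complications) were included as secondary study endpoints". Section 2.1 describes the complications to be prevented as arising during ablation as well as after it.

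The decision rule in section 5.4 reads "Non-inferiority is demonstrated if the upper bound of the 95% CI for the risk difference is below" the margin of 0.8%, with a Farrington-Manning interval. It does not say which of the two sets decides, or whether both must pass. The only other rule on PP membership, under Missing Data, concerns patients lost to follow-up before an event.

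**The concern.** Membership of an analysis set should not depend on the outcome that the set is used to compare. Here an embolic event during the procedure can be the reason why ablation was not completed, and completion is the condition for entering PP. The event then deletes the patient, and itself, from the analysis.

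In a non-inferiority trial the PP analysis is normally the guard against a diluted difference. With a fixed absolute margin, losing the same proportion of events from both arms shrinks the true difference and narrows the interval, so PP can pass more easily without any imbalance in the loss. The expected number of events is small enough for a single deletion to matter.

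**Working it through.** **Inputs.** Section 3.2 gives ICE 0.6%, TEE 0.5%, margin 0.8%, one-sided alpha 0.025 (z = 1.96) and 1810 patients recruited. Allocation is 1:1 (section 4.1), so 905 per arm. The interval method is Farrington-Manning (section 5.4). The share of events that stop an ablation is not given; it is treated below as an assumption, f.

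**The plan's own figure.** The protocol gives no figure on this point. Its sample-size arithmetic reproduces closely: 7.84 × (0.006 × 0.994 + 0.005 × 0.995) / 0.007² = 1750.24, against 1750.45 stated, and 1750 / 0.98 = 1786. Whether that n is a total or a per-group number is a separate matter and is not used here.

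**Expected events.** 905 × 0.006 = 5.4 in ICE and 905 × 0.005 = 4.5 in TEE, about 10 in all.

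**One event more or less.** The rule passes when z = (RD − 0.8%) / SE is below −1.96, with SE taken from the rates fitted under a true difference of 0.8%.

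- ICE 5/905 v TEE 4/905: RD = 0.110%, fitted rates 1.095% and 0.295%, SE = √[(0.010948 × 0.989052 + 0.002948 × 0.997052) / 905] = 0.390%. z = (0.110 − 0.8) / 0.390 = −1.77, so it fails.
- Without one ICE patient who had an event, 4/904 v 4/905: RD = 0.0005%, SE = 0.385%, z = −2.08, so it passes.

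Solving for the difference at which z = −1.96 gives the upper limits:

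| ICE v TEE events | Upper limit, all kept | Patient removed | Upper limit after |
|---|---|---|---|
| 5 v 4 | 0.90% fails | one ICE | 0.74% passes |
| 4 v 3 | 0.84% fails | one per arm | 0.77% passes |
| 6 v 6 | 0.86% fails | one ICE | 0.705% passes |
| 6 v 6 | 0.86% fails | one per arm | 0.801% still fails |
| 6 v 6 | 0.86% fails | one TEE | 0.95% fails by more |
| 4 v 4 | 0.74% passes | one TEE | 0.84% fails |

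A single removal can therefore reverse the PP result in either direction.

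**False-pass probability at the margin.** Take true rates of 1.3% (ICE) and 0.5% (TEE), a difference of exactly 0.8%. If a share f of patients with events leaves PP, the rate p becomes p(1 − f) / (1 − pf). At f = 20% in both arms, ICE becomes 0.0104 / 0.9974 = 1.043% and TEE 0.0040 / 0.9990 = 0.400%. The apparent difference falls to 0.64%, inside the margin. Exact binomial sums over all event counts, at 905 per arm, give:

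| Assumed loss of events | Probability of declaring non-inferiority |
|---|---|
| none | 1.9% |
| 2% in both arms | 2.1% |
| 5% in both arms | 2.3% |
| 10% in both arms | 2.8% |
| 20% in both arms | 4.2% |
| 20% in ICE only | 6.7% |
| 20% in TEE only | 1.1% |

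The nominal level is 2.5%. Equal loss stays under it at 5% and exceeds it at 10%.

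**The case against.** The strongest case on the other side has four parts.

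**The wording may only mean adherence.** The PP entry can be taken to mean that the patient received the assigned strategy without crossover or major violation, and finer membership rules are often left to the statistical analysis plan. That intent is plausible. But the protocol has stated a rule, its verb differs from the one used for mITT, and nothing in the document prevents the literal reading. The Missing Data rule fits an intent to keep patients with events, but it covers loss to follow-up only.

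**The mITT set keeps these patients.** On its natural reading it does, because it asks only that ablation was undergone. A disagreement between the two sets would also be visible. This stands, and it confines the problem to PP.

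**The direction is not fixed.** A reader might infer that the wording pushes the trial towards non-inferiority. The documents do not support that as a general statement. It holds for equal proportional loss or loss weighted to ICE. Loss mainly from TEE does the opposite, and nothing in the protocol says which arm would lose more.

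**The size is unknown.** Only events that occur during ablation and stop it are affected. Follow-up runs to 1 month (section 5.1), and patients with events after a completed ablation stay in PP. With about 10 events expected, a 20% loss means about two patients. At 2% to 5% equal loss the false-pass probability stays below nominal.

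A reader might also count procedures stopped for tamponade or bleeding. Those are secondary endpoints (sections 3.5 and 8.2), so such a patient is not excluded by the primary outcome itself, although a later embolic event in that patient would still be lost from PP under the same wording.

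**Conclusion.** The defect is real and limited. As written, PP membership can be decided by the primary outcome, and with about 5 expected events per arm one such exclusion can reverse the PP conclusion. Under equal loss of 5%, 10% and 20% the false-pass probability at the margin is 2.3%, 2.8% and 4.2%, against 1.9% with all events kept; with 20% lost from TEE only it is 1.1%.

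These figures rest on 905 patients per arm, the Farrington-Manning rule and assumed loss shares. The documents fix neither the size nor the direction of the effect, and they do not show that the trial's overall conclusion is biased, since mITT is unaffected. How much the PP result matters also depends on the role it is given, which section 5.4 leaves open. Severity is minor to moderate: worth correcting before analysis, but not a fault that undermines the design.

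**What to change.** In section 5.4 Statistical Methods, define the PP set as patients who had the assigned screening test and in whom ablation was started, without major protocol violations. Add one sentence: a primary-endpoint event, or stopping the procedure because of one, is never in itself a reason for exclusion from PP.

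The change is to the analysis-set definition only. It needs no new data and alters nothing in the conduct of the procedure. The cost is a PP set slightly closer to mITT. It should be made before outcomes are known by arm, so that the reading of completion cannot be chosen in the light of the events.
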